## Abstract

**Background:**

Most opioid use disorder (OUD) treatment guidelines target community medical settings, and the subsequent recommendations were established to prioritize safety and reduce diversion prior to the fentanyl era. For people with OUD who use unregulated fentanyl, slow induction onto opioid agonist therapy (OAT) with gradual dose titration is often ineffective or insufficient for reducing withdrawal symptoms and cravings, thereby hampering engagement and retention in treatment. Given the severe risks associated with continued use of the increasingly toxic unregulated drug supply, new and innovative approaches to the management of OUD are urgently needed. We have developed an alternative induction protocol, using a rapid intravenous symptom-inhibiting fentanyl induction (SIFI) to optimize rotation onto oral OAT.

**Methods:**

An open-label, single arm, prospective pilot clinical trial is being conducted in an outpatient setting to assess the safety, feasibility, and efficacy of a rapid symptom-inhibiting intravenous fentanyl induction protocol to establish starting doses of methadone or sustained-release oral morphine (SROM) based on individual opioid requirements, as a treatment strategy for individuals with OUD who use unregulated fentanyl. The primary outcome is safety, as defined by occurrence of study drug-related adverse events (including but not limited to opioid toxicity and QT interval prolongation) that require intervention during induction and the first 7 days on OAT. Secondary objectives are to determine whether the SIFI protocol will result in use of higher-than-standard starting doses of methadone and SROM, and to determine whether implementation of this protocol will be acceptable to participants and will result in reduced withdrawal symptoms, improved retention, and better long-term outcomes on OAT.

**Discussion:**

This is the first study to rapidly and objectively estimate opioid tolerance and use it to calculate individualized starting doses of oral OAT in an outpatient setting among people who use unregulated fentanyl. We predict that starting methadone or SROM with individually-tailored doses will lead to therapeutic target concentrations being achieved quickly, safely, and with good patient satisfaction. This approach has the potential to more effectively and safely initiate OAT, to minimize opioid withdrawal and cravings, and in turn to decrease unregulated fentanyl use and increase retention on life-saving OAT.

**Trial registration:**

ClinicalTrials.gov, NCT05905367; date of registration: June 15, 2023; latest update posted July 18, 2024. https://clinicaltrials.gov/study/NCT05905367

*Protocol version*: 4.0, April 22, 2024.

**Supplementary Information:**

The online version contains supplementary material available at 10.1186/s13722-025-00586-7.

## Background

Canada is facing an escalating epidemic of unregulated drug overdoses, with fatalities in unprecedented numbers. More than 42,000 opioid toxicity deaths occurred in Canada between January 2016 and September 2023 [1]. The province of British Columbia (BC) is the most severely affected, with an annual rate of 45.3 opioid toxicity deaths per 100,000 population compared with the Canadian average of 19.4 per 100,000 population in 2022 [1].

The major driver of the ongoing crisis of drug overdoses and deaths is the increasing toxicity of the unregulated drug supply, fueled by fentanyl and its analogues. Fentanyl, a potent opioid agonist, was developed in the 1950 s to fill a need for strong and rapid analgesia. Because of these characteristics, fentanyl is commonly used to treat chronic cancer pain or in anesthesia [2]. Initially present as an adulterant in unregulated drugs, especially heroin, fentanyl is now the substance of choice for many people with opioid use disorder (OUD) [3].

The harms associated with fentanyl use are related to its high potency and short duration of action, leading to very frequent use, severe cravings, and more difficult to manage withdrawal symptoms [2, 4, 5]. Fentanyl was involved in 82% of Canadian opioid toxicity deaths in 2023 [1]. In BC, fentanyl was detected (alone or in combination with other drugs) in 86% of unregulated drug toxicity deaths in 2021, a striking increase from 5% in 2012 [6].

Opioid agonist therapy (OAT) has been shown to be safe and effective for the treatment of OUD. When prescribed in therapeutic doses, OAT decreases morbidity and mortality due to overdose and other OUD-related harms including serious acute and chronic infections including human immunodeficiency virus (HIV) and hepatitis C [7]. However, the shift to fentanyl in the unregulated drug supply has significantly complicated the management of OUD. People who use fentanyl experience severe withdrawal symptoms, often compromising OAT initiation, retention and adherence [4, 8].

Effective OAT doses are highly variable, depending on a number of factors, including the individual’s opioid tolerance and interindividual variability in pharmacokinetics [9]. Unfortunately, assessment of opioid tolerance is challenging, and is typically subjective, relying on the patient’s self-report of the amount and frequency of their opioid use, and is further complicated by the unpredictability of the unregulated drug supply [4]. Unknown opioid tolerance increases the risk of opioid overdose with OAT, and sequential administration of methadone without reaching steady state may cause “dose stacking” and the potential for dose accumulation [10]. In view of these risks, current North American OUD treatment guidelines (developed when heroin was the dominant opioid in the unregulated market) take a cautious approach, recommending low starting doses and slow, gradual dose increases [7, 11]. The British Columbia Centre on Substance Use (BCCSU) and Ontario’s Mentoring, Education, and Clinical Tools for Addiction: Partners in Health Integration (META:PHI) initiative have updated their guidance to reflect the changing unregulated drug market, providing recommendations for more rapid, albeit still conservative methadone initiation and titration [10, 12].

However, as previously noted, fentanyl is highly potent and is being used in large doses. As a result, currently recommended oral OAT induction protocols provide an inadequate speed of OAT titration for a large proportion of individuals with OUD who use unregulated fentanyl. Prescribing OAT according to current recommendations is frequently associated with persistence of severe and recurrent cravings and withdrawal symptoms over the weeks to months before therapeutic target levels of OAT can be reached, with ongoing unregulated substance use during the lengthy titration period [4, 8]. Indeed, a recent analysis of BC health administrative datasets including more than 55,000 people with OUD showed that, while OAT engagement and retention were protective against hospitalization and death, methadone initiation in compliance with current clinical guidelines was associated with increased risk of death or hospitalization within the first 6 months [13]. Even maximum recommended OAT doses are often inadequate to meet the opioid requirements of people who use fentanyl, leading to poor retention in OAT programs and continued use of unregulated drugs, with their attendant risks of overdose and death, even among those who remain on OAT [4, 13, 14].

In an attempt to address this issue in the context of managing hospitalized individuals who use fentanyl, we pioneered a novel alternative induction protocol using a rapid intravenous symptom-inhibiting fentanyl induction (SIFI) for objectively determining opioid tolerance using medically-administered intravenous (IV) fentanyl [3]. Implementation of the SIFI protocol in hospitalized patients with OUD has proven feasible, safe, and effective in meeting the patients’ opioid requirements, and thereby effectively managing opioid withdrawal and averting patient-initiated discharge from hospital against medical advice. Herein we propose to conduct the first evaluation of the safety, efficacy, and acceptability of the SIFI protocol in an outpatient setting.

To this end, we will implement and evaluate our rapid IV fentanyl induction protocol among patients who use fentanyl and who are receiving services at Hope to Health, a community primary care clinic located in the Downtown Eastside neighborhood of Vancouver, the epicenter of the unregulated drug use epidemic in Canada.

In brief, we will use each individual’s calculated opioid tolerance to guide their transition onto OAT with oral methadone or sustained-release oral morphine (SROM), with the choice of agent based on a shared decision-making process between the patient and their clinician. Methadone or SROM starting doses will be individualized based on an objective assessment of the patient’s opioid requirements (with defined upper dose limits in the interests of safety), thus achieving therapeutic target levels more quickly than with standard OAT dosing according to current OUD treatment guidelines. We anticipate that opioid withdrawal and cravings will thus be more effectively managed, leading in turn to improved acceptability and retention on OAT.

## Study design

### Overview of study design

To assess the safety, feasibility, and efficacy of a rapid symptom-inhibiting IV fentanyl induction (SIFI) protocol, we plan to conduct an open-label, single arm, prospective clinical trial with a planned sample size of 50. The primary goal of this pilot study is to identify unforeseen problems with the SIFI procedures that would impact participant safety. If such a problem exists with a prevalence of 5% (i.e. potential to affect 1 out of 20 participants), it will be identified with 92% confidence in a pilot study including 50 participants [15].

Results of this pilot study will be used to inform a subsequent larger and more comprehensive investigation of the SIFI protocol as a treatment strategy for individuals with OUD who intentionally use unregulated fentanyl.

### Study objectives

The primary objective is to assess the safety and feasibility of an outpatient SIFI protocol for determining individualized starting doses of oral OAT with methadone or SROM. Safety will be assessed in the first instance by a descriptive analysis of adverse events (e.g. sedation, respiratory depression, hypoxia, QT prolongation) requiring intervention during the induction/maintenance period (study days 1 through 7).

Secondary outcomes include starting OAT doses, participant satisfaction, and presence of withdrawal symptoms, OAT retention, overdose, hospitalization, and death at 1 and 3 months. Longer term impact of the strategy will be assessed at 6 and 12 months post-induction. Secondary outcomes will be reported using descriptive and summary statistics. Participants’ responses to the treatment satisfaction questions will be reported qualitatively, and used to refine the SIFI procedure for future investigation.

### Study setting

The opioid overdose crisis has disproportionately affected under-served communities, including those with low socioeconomic status and complex medical and mental health issues. This study will be conducted at the Hope to Health Research and Innovation Complex in Vancouver’s Downtown Eastside (DTES), a neighborhood of approximately 18,000 residents with high rates of poverty, homelessness, mental illness, and drug use [16]. Residents of the DTES are disproportionately impacted by the ongoing opioid overdose crisis: in 2023, the rate of overdose deaths per 100,000 population in the DTES was 560.9, which was ten times higher than in the rest of the city of Vancouver (56.7) or in the province of BC as a whole (46.5) [17].

Hope to Health is an integrated facility that includes a low-barrier interdisciplinary Primary Care Clinic which currently supports 2800 active clients, and a co-located Supervised Consumption Site. The Supervised Consumption Site handles approximately 1000 visits per month, of which 90% involve use of opioids with or without other substances. This is a nurse- and peer-led service offering safe spaces to use unregulated or prescribed substances, as well as distributing harm reduction supplies and offering nursing care and referrals to the Primary Care Clinic or other services, as needed. Both the Primary Care Clinic and the Supervised Consumption Site support a safer drug supply program that offers clients the possibility of replacing their unregulated drug supply with prescribed pharmaceutical grade alternatives, including hydromorphone tablets or fentanyl patches.

### Recruitment

Study participants will be recruited from the Hope to Health Primary Care Clinic and the adjacent Supervised Consumption Site. The planned sample size of 50 should be feasible based on the number of clients who are currently registered in the Hope to Health Primary Care Clinic who have a diagnosis of OUD and who do not have an active OAT prescription or who are receiving a suboptimal OAT dose (based on their continued use of unregulated fentanyl). In addition, the clinic continues to register new clients from the DTES population where OUD and fentanyl use are highly prevalent, including referrals from the adjoining Supervised Consumption Site where over 90% of visits involve use of opioids with or without other substances.

The clinic medical team will identify clients who are potential candidates for OAT, based on a diagnosis of OUD, ongoing active use of unregulated street drugs, and the client’s goal to decrease their opioid use. With the client’s approval, the clinic team member will introduce the client to the study coordinator, who will explain the study and seek their informed consent to participate. Written informed consent will be obtained from each prospective participant prior to their undergoing any study-related procedures. A research team member who is not directly involved in the client’s care will review and explain the study protocol and informed consent form with the prospective participant. It will be made clear that their participation is voluntary and that they are free to choose not to participate, or to withdraw from the study at any time, without affecting their access to clinic services or the quality care they receive at the Hope to Health Primary Care Clinic. The study procedures and reasonably foreseeable risks and potential benefits will be explained in detail. After the client has had adequate time to read the REB-approved consent form (or have it read and explained to them) and has had any questions answered to their satisfaction, if they agree to participate they will sign the consent form in a private office in the presence of the person who discussed the study with them.

After informed consent has been obtained and screening evaluations (Table 1) have been completed, research staff will review the inclusion/exclusion criteria and determine the potential participant’s eligibility for the study.

**Table 1 Tab1:** Schedule of assessments during screening and IV fentanyl induction phase on Day 1

	Screening	Day 1 before start of induction	5 min after each IV fentanyl dose	5, 10, and 15 min after last IV fentanyl dose
Informed consent	x			
Medical history	x			
Medication review	x			
UDT	x			
Pregnancy test^a^	x	(x)^b^		
Height, weight		x		
Record time of last opioid use		x		
ECG		x		
POSS		x	x	x
COWS		x	x	
HR, BP, RR, SpO2		x	x	x
Participant-readiness threshold		x		
MSQ for OUD meds	x	(x)^b^		

*IV* intravenous, *UDT* urine drug test, *ECG* electrocardiogram, *POSS* Pasero opioid-induced sedation scale, *COWS* clinical opiate withdrawal scale, *HR* heart rate, *BP* blood pressure, *RR* respiratory rate, *SpO2* oxygen saturation, *MSQ* Medication Satisfaction Questionnaire, *OUD* opioid use disorder

^a^For individuals of child-bearing potential

^b^If screening and baseline not on same day

### Study population

#### Inclusion criteria

Age 19 years or olderOUD of any severity by DSM-5 Clinical Diagnostic criteria [18]Intentional use of unregulated fentanyl by any route (e.g. injection, inhalation) by participant self-reportUrine drug test (UDT) positive for fentanyl at screening or within 7 days prior to date of screening visit, to confirm the presence of fentanylClinical indication to start OAT with methadone or SROM, or recently started OAT and receiving daily doses of methadone ≤ 150 mg or SROM ≤ 1300 mg (demonstrated to be subtherapeutic for the individual as they are continuing to use unregulated fentanyl)If taking prescribed opioids for safer supply, willing to discontinue them starting on study Day 1 and for at least the first 7 days of the studyWilling and able to provide written informed consent for study participation

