#### Exclusion criteria

Individuals who are pregnant or breast-feedingCurrently receiving prescribed fentanyl in any form, e.g. fentanyl patchPrevious participation in this study (previous receipt of SIFI in an in-hospital clinical setting is not exclusionary)Current use of buprenorphine extended-release (Sublocade®) in any doseUse of buprenorphine-naloxone (Suboxone®) within the previous 3 days

Potential participants will not be excluded based on presence of substances other than fentanyl in the screening UDT, nor on the basis of alcohol use disorder or any other substance use disorder. The intent is to make the protocol applicable in a real-world setting where the majority of individuals who have OUD use multiple other substances in addition to opioids.

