### Early OAT phase

The specific OAT agent will be chosen prior to study enrolment by the clinic medical team in conjunction with the participant. To determine the first post-induction dose of OAT, the loading dose of fentanyl will be multiplied by 8 and used as a proxy for the participant’s opioid tolerance over 24 h. The multiplier of 8 in this calculation is based in part on anecdotal patterns of unregulated opioid use from the investigators’ experience—approximately 8 times per day. Since the protocol assessment of opioid tolerance reflects a single use, the multiplier of × 8 estimates total daily use. In addition, this approach aligns with the known duration of analgesia and respiratory depression from IV fentanyl boluses, which potentially last 1.5 to 4 h [23]. The calculated opioid tolerance will then be converted to the starting dose for methadone or SROM (Figs. 2 and 3), up to a maximum daily dose of 200 mg or 2000 mg, respectively. From the investigators’ clinical experience utilizing the SIFI protocol in an inpatient setting, participants are generally comfortable for approximately 1–3 h following induction [3], allowing adequate time for calculation, preparation, and dispensing of the individualized starting dose of OAT.

The first on-study oral OAT dose will be administered on the same day as the induction procedure and at least 15 min after the final IV fentanyl dose. On Day 1, participants will receive a maximum total methadone dose of 200 mg or a maximum total SROM dose of 2000 mg, adjusting for any previously prescribed methadone or SROM they received on Day 1 prior to arrival at the clinic. After the post-induction OAT dose is administered, the participant will remain in the clinic for 3 h under observation for ongoing monitoring of safety and vital signs (Table 2), and will receive a cash honorarium for their participation and for the time spent at the clinic. Thereafter, the participant will be offered honoraria for attendance at daily study visits for 7 days for assessment and OAT dispensing (Table 2). If the participant is found to be over sedated (POSS 3 or 4), reports sleeping more than usual, or exhibits any other signs or symptoms of excessive opioid levels, they will be referred to the clinical team for immediate assessment and management, including adjustment of OAT dose if deemed clinically necessary.

**Table 2 Tab2:** Schedule of assessments during early OAT phase (Day 1 through Day 7)

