Another potentially confounding factor in the calculation of opioid tolerance could be the presence of buprenorphine, an opioid partial agonist that is sometimes prescribed for the treatment of OUD. While current use of either buprenorphine extended-release (Sublocade®) or buprenorphine-naloxone (Suboxone®) is exclusionary in our protocol, it should be noted that buprenorphine extended-release (Sublocade^®^) has a long terminal half-life and relevant plasma concentrations can be maintained for up to 5 months after the last administration [35, 36]. If the SIFI protocol were to be implemented in a setting where these agents are in regular use, it may be prudent to ensure a 5-month interval has passed since the last Sublocade^®^ dose or to ensure buprenorphine is absent during urine drug testing, to mitigate the confounding effects of residual buprenorphine on the assessment of opioid tolerance using IV fentanyl.

We expect that application of the SIFI protocol will result in higher-than-standard starting doses of oral OAT. Accordingly, in the interests of participant safety and to prevent early withdrawal after OAT initiation, every effort will be made to ensure the protocol-planned assessments are completed during the 3 h after the first dose of OAT and the first 7 days thereafter. Participants will be offered an honorarium for remaining in the clinic for a full day including participation in the induction and 3 h of assessment time following the first OAT dose. Honoraria will also be provided for participants returning to the study clinic for daily assessments during the first week on OAT.

We expect that the potential harms associated with IV fentanyl induction and high-dose methadone or SROM in this protocol will thus be minimized, especially when compared to the known harms associated with OAT dropout and continued use of the unregulated drug supply. We predict that tailored starting OAT doses will lead to therapeutic target levels being achieved more quickly, thereby more effectively managing opioid withdrawal and cravings, and in turn leading to increased retention on life-saving OAT and decreased reliance on the toxic street drug supply. We believe the findings of this study will be generalizable to other clinical settings, particularly in jurisdictions where fentanyl use is widespread.

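### The 'higher-than-standard starting dose' objective covers people already on methadone or SROM, for whom the first study dose is a dose change and not a start

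*Protocol article*

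**What the plan says.** The trial is described as a "single arm, prospective clinical trial with a planned sample size of 50" (Overview of study design).

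**Objective and outcome.** The Abstract (Methods) gives as a secondary objective whether SIFI will "result in use of higher-than-standard starting doses of methadone and SROM". The Secondary outcomes section lists the starting dose of oral OAT once, without separating participants by what they were taking at entry. Study objectives and Data analysis and management say only that secondary outcomes are summarised descriptively.

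**Who may enter.** The Inclusion criteria cover people with an indication to start OAT. They also cover people "recently started OAT and receiving daily doses of methadone" of 150 mg or less, or SROM of 1300 mg or less, who still use unregulated fentanyl. The Recruitment section counts clients on a suboptimal OAT dose when it argues that 50 participants can be found.

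**How the dose is set.** Under Early OAT phase, the total IV fentanyl given at induction is multiplied by 8 to stand for 24-hour tolerance. It is then converted to methadone or SROM, with maxima of 200 mg and 2000 mg. Existing OAT appears only in the Day 1 total, "adjusting for any previously prescribed methadone or SROM they received on Day 1 prior to arrival at the clinic".

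**Buprenorphine.** The Exclusion criteria rule out current use of the extended-release form, and buprenorphine-naloxone within 3 days. They add: "Potential participants will not be excluded based on presence of substances other than fentanyl in the screening UDT". The Discussion calls buprenorphine a potential confounder of the tolerance calculation and says of the extended-release form that "relevant plasma concentrations can be maintained for up to 5 months after the last administration".

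**The concern.** The objective presupposes that each participant is starting OAT, but the eligibility criteria do not. For someone already taking methadone or SROM, the first study dose is a change from an existing dose. Comparing it with a standard starting dose does not answer the question asked. If the objective is followed as printed, such people can count as evidence that SIFI led to higher starting doses.

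The loading dose also means something different in the two groups. In a person with no OAT on board it reflects the opioid needed for comfort. In a person who has methadone or SROM on board it reflects the need on top of that opioid. The text applies the same multiplier of 8 to both. The Discussion considers sedatives, stimulants and buprenorphine as influences on the tolerance estimate, but not the full-agonist OAT that the entry criteria admit by design.

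What is at stake is the reading of the first-listed secondary outcome and of the loading dose. The Overview says the pilot will inform a larger study, so a dose result that cannot be interpreted would be carried into its planning. With a single arm, no control group shares the same mix of entry states.

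**Working it through.** **1. The plan's own figure.** The sample-size statement says of a problem with 5% prevalence that "it will be identified with 92% confidence in a pilot study including 50 participants". With n = 50 and p = 0.05: 1 − 0.95^50 = 1 − 0.077 = 0.923. The stated 92% is reproduced. The present point does not depend on it.

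**2. Entry ceilings against study maxima.** Inputs are from Inclusion criteria and Early OAT phase.
- Methadone: 150/200 = 75%.
- SROM: 1300/2000 = 65%.

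These are limits, not typical doses. They show only that a participant may enter on a large part of the highest study dose.

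**3. Where existing OAT enters the calculation.** The chain in the text is loading dose, × 8, conversion, cap. The entry dose is not an input to the first three steps as described. It appears only when the Day 1 total is limited. The conversion figures (Figs. 2 and 3) are not available here, so any allowance made in them cannot be checked.

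**4. Direction.** Two effects are possible.
- OAT on board may reduce the fentanyl needed for comfort, which lowers the × 8 figure and the calculated dose. The Discussion reasons this way about other sedating factors.
- Being on OAT and still using fentanyl may mark higher tolerance, which raises the calculated dose.

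The article does not settle which dominates.

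**5. Sensitivity of a single overall percentage (assumptions only).** Let f be the share of all participants whose entry dose already exceeds the standard start and whose study dose is not lower than their entry dose. Let q be the share above standard among the remainder, taken to behave like new starters. If everyone is reported together, the share above standard is f + (1 − f)q.

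| f | q = 0 | q = 0.50 |
|---|---|---|
| 0.10 | 10% | 0.10 + 0.90 × 0.50 = 55% |
| 0.25 | 25% | 0.25 + 0.75 × 0.50 = 62.5% |
| 0.50 | 50% | 0.50 + 0.50 × 0.50 = 75% |

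The article gives no value for f, for q, or for the standard dose. The table shows how far an overall figure could depend on the entry mix; it does not estimate what will happen.

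**6. Buprenorphine, passages side by side.** The exclusion is tied to current extended-release use and sets no interval since the last dose. The Discussion puts relevant concentrations at up to 5 months. A former user inside that window is therefore eligible as written, and other findings in the screening urine test do not exclude. The Discussion offers a 5-month interval or a negative urine test only as possible precautions for settings where these agents are in regular use.

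**The case against.** The strongest reply is that the article nowhere says the two entry groups will be analysed together. It calls the analysis descriptive, and table layout belongs to a full protocol or SAP that is not shown. That stands: a single combined summary is an inference. It does not remove the point, because the mismatch lies in the printed objective, outcome and entry criteria. A subgroup table in another document would still leave the objective applying a starting dose to people who have already started.

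A reader might infer that a higher-than-standard result is built in at entry. The text does not support this. The study dose is computed from the fentanyl loading dose and not carried forward from the earlier prescription, and step 4 shows that the effect could run either way.

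A reader might also infer that the trial estimates the fentanyl-to-OAT conversion in a confounded mixture. It does not: the conversion is fixed in advance.

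Nor is there a flat contradiction on buprenorphine. The Discussion discloses the residual-drug issue and words it as a possibility. What stands is that the exclusion leaves uncovered a period which the same article identifies as potentially confounding.

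Finally, mixed entry is deliberate and openly stated, and the trial is a pilot with a safety primary outcome. This limits the weight of the point.

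**Conclusion.** The point holds for the secondary dose objective and for interpreting the loading dose. As printed, the objective cannot be answered in participants already on OAT at entry. Their loading dose is not comparable with that of new starters unless existing OAT is accounted for, and the text describes no such step for the tolerance estimate.

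The size cannot be derived. The 75% and 65% ratios are ceilings, and the range of 55% to 75% in step 5 rests wholly on assumed f between 0.10 and 0.50 with q = 0.50. It would be tempting to say how many of the 50 will falsely count as high starters. The article gives no share entering on OAT, and not everyone who does would already be above a standard start. The direction is also open.

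There is no numerical error. The primary safety outcome and N = 50 are unaffected. The change is worth making before results are summarised, but it is not a condition for the trial's main conclusion.

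**What to change.** - Report loading dose, first study dose, COWS and retention separately for participants on OAT and not on OAT at entry.
- Evaluate the higher-than-standard starting dose objective only in participants not on OAT at entry. In the others, report the change from the pre-study daily dose.
- Record any OAT taken on Day 1 before induction; the Day 1 adjustment already requires this to be known.
- Record the date of the last extended-release buprenorphine dose and the urine result for buprenorphine. Show loading-dose results with and without participants inside the 5-month window named in the Discussion.
- Reconcile the Exclusion criteria with the Discussion on residual buprenorphine. No clinical rule is proposed here.

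**Cost.** Medical history, medication review and urine testing are already scheduled (Table 1), so this means extra table columns and one history item. The article does not say whether the urine panel covers buprenorphine; if it does not, that is a further small item.

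The real price is smaller groups. If 20% to 60% of the 50 enter on OAT (an assumption), that is 10 to 30 people, leaving 40 to 20 new starters. For an observed proportion of 50%, the approximate 95% half-width is 1.96 × √(0.25/n): 14 percentage points at n = 50, 15 at n = 40 and 22 at n = 20. As no hypothesis test is planned for these outcomes, no stated power is lost.
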